**7. DESIGN OF THE STUDY**

The study is designed as a open, parallel group, randomised controlled intervention study.

7.1 Patients

7.1.1 Inclusion and exclusion criteria

Inclusion criteria are:

- patients treated by HD 2 or 3 times a week, for at least 2 months.
- patients able to understand the study procedures.
- patients willing to provide written informed consent.

Exclusion criteria are:

- current age < 18 years*
- treatment by HDF or high flux HD in the preceding 6 months
- severe incompliance**
- life expectancy < 3 months due to non renal disease
- participation to other clinical intervention trials evaluating cardiovascular outcome***

* In Europe, the median age at the start of HD therapy was 60 years (proportion of new HD-patients 60-69 yr: 25%, >70 yr: 27%).[[111]](#endnote-112) Thus, *chronic* HD patients tend to be still older. Since the study results might be of importance for HD patients of all ages, it seems irrational to exclude patients > 70 years. Thus, no upper age limit is applied.

** severe non-adherence to the dialysis procedure and accompanying prescriptions, especially frequency and duration of dialysis treatment and fluid restriction.

*** Participation of patients to other (e.g. observational) studies will be discussed with and decided by the executive committee.

# 7.1.2 Participating centers

All dialysis centres which are able to perform on-line hemodiafiltration in the Netherlands will be asked to participate in the study to obtain a total patient number of 772.As of yet, 17 centres have agreed to participate in the study. Participating centres should include a minimum of 10 patients.

**7.2 Study approach**

7.2.1 stabilisation period

Before randomisation, patients will be dialysed on low-flux synthetic dialysers. During this period, treatment times will be determined in order to achieve an adequate dialysis dose, according to DGN-standards (target dialysis spKt/V ≥ 1.2/treatment).

7.2.2 randomisation

As soon as patients are considered to be ‘stable’, patients will be randomized by the Julius Center Randomisation office. Patients will be randomized into a 1:1 ratio for treatment with on-line hemodiafiltration (HDF) or continuation of treatment with low-flux hemodialysis (HD) during 3 years. Randomisation will take place stratified by participating clinic.

**7.3 End points**

7.3.1 Primary end points

- non-fatal and fatal cardiovascular events
- all cause mortality

7.3.2 Secondary end points

Changes in:

- carotid intima media thickness (cIMT)
- aortic pulse wave velocity (PWV)
- left ventricular mass index (LVMi)
- interdialytic blood pressure
- laboratory assessments (routine – according to DGN guidelines; oxidative stress; acute phase response; lipid profile; various)
- quality of life (QoL)
- nutritional state

**7.4 Practical implementation**

7.4.1 Stabilisation period

*7.4.1.1 Hemodialysis:* patients will be dialyzed 3 times (or 2 times) a week with a synthetic low-flux membrane (UF-coefficient < 12 ml/mmHg/h, sterilization by steam or γ-irradiation) during the stabilisation phase. Blood flow will be maintained at 250-300 ml/min. Anticoagulation is performed with low molecular weight heparin (LMWH) before HD. Patients on coumarins will receive 50% of the LMWH dose. Treatment times will be adapted to a target dialysis spKt/V urea of ≥1.2 / treatment.

*7.4.1.2 Dialysate:* Ultrapure water is used for preparation of dialysis fluid. Bicarbonate is provided from powder cartridges to avoid the risk of a bacterial load from bicarbonate concentrates. For instance, the biBAGR system (Fresenius) and BiCartR system (Gambro) will be used. The dialysate flow is 500 ml/min in HD. The temperature of the dialysate is 36oC.

*7.4.1.3 Metabolic control:* metabolic control will be performed according to the guidelines of the Nederlandse Federatie voor Nefrologie / Kommissie Kwaliteitsbewaking (NFvN/KK: anemia / calcium- and phosphate levels / acidosis).

*7.4.1.4 Medication:* antihypertensive medication, lipid lowering therapy, inhibition platelet aggregation and medication to treat renal anemia and renal osteodystrophy will be prescribed according to the NFvN/KK guidelines, and if not available according to common practice.

*7.4.1.5 Randomisation:* After the stabilisation period, patients will be randomised centrally to either treatment with low-flux HD, or treatment with on-line HDF (1:1). Stratification will be performed for the participating centres.

7.4.2 Study period

*7.4.2.1 Hemodialysis:* HD treatment, as performed in the stabilisation period, will be continued.Treatment times will be adjusted only of dialysis spKt/V urea < 1.2 / treatment.

*7.4.2.2 Hemodiafiltration:* Patients will be treated with (on-line) HDF, target dose postdilution 6 l/h (~100 ml/min) and a high-flux synthetic dialyser (UF-coefficient > 20 ml/mmHg/h, sterilization by steam or γ-irradiation). Blood flow, anticoagulation and treatment times will be fixed according to the prescription in the stabilisation period. If the blood flow is less than 300 ml/min, the postdilution volume will be decreased accordingly (filtration and postdilution <33% of blood flow). If necessary, LMWH will be given in two separate doses. The treatment time will be adjusted only when spKt/V urea is < 1.2 / treatment.

*7.4.2.3 Metabolic control:* see ‘stabilisation period’.

*7.4.2.4 Medication:* see ‘stabilisation period’.

# 7.4.3 Dialysis procedure:

##### 7.4.3.1 Dialysate: ultrapure water is used for preparation of bicarbonate-containing dialysis fluid, which undergoes one step of ultrafiltration converting it into ultrapure dialysis fluid. Dialysis fluid is produced at a rate of 600-800 ml/min of which approximately 100 ml/min is diverted for further processing into substitution fluid. The electrolyte composition of the dialysis fluid is: Na 138-140 mmol/l; K 1.0-3.0 mmol/l; HCO3 30-35 mmol/l; Ca 1.0-1.7 mmol/l; Mg 0.5 mmol/l; Cl 108-109.5 mmol/l; glucose 0-5.6 mmol/l; acetate 3 mmol/l.

*7.4.3.2 Infusate/ the on-line system:* The substitution fluid is prepared from the dialysis fluid by one additional step of controlled ultrafiltration, before it is infused post-filter into the blood. The electrolyte composition of the substitution fluid is the same as the composition of the dialysis fluid. Ultrafiltration procedures will be performed according to the manufacturers’ instructions. For instance:

- the on-line system, ONLINEplus™ (Fresenius Medical Care, Bad Homburg, Germany) is integrated into the dialysis machine (4008 series; Fresenius Medical Care) and consists of two ultrafilters (DIASAFE® plus), an infusate pump module, and disposable infusate lines. Infusate is prepared continuously by double-stage ultrafiltration. Both filters are subjected to automated membrane integrity tests before dialysis, and are replaced after 3 months of use. Dialysis fluid downstream from the first filter stage enters the dialyser; part of the stream is subjected to cross-flow filtration in the second filter in order to produce infusate. The infusate stream is connected with the venous bubble catcher for post-dilutional HDF.

- an AK 100/200 ULTRA dialysis machine (Gambro AB, Lund, Sweden) prepares ultrapure water and ultrapure dialysis fluid by stepwise ultrafiltration of water and bicarbonate –containing dialysis fluid (BiCart) using two polyamide ultrafilters (U 8000 S). When used for HDF, sterile non-pyrogenic solution is prepared on-line from the ultrapure dialysis fluid by an additional step of ultrafiltration using a sterile polyamide ultrafilter (U2000) integrated in a sterile line set (Steriset). The hygiene of the fluid pathway, including the U8000S ultrafilters, will be assured by heat disinfection after each treatment. The U8000S filters are changed bimonthly. The final ultrafilter (U2000) is employed on a single-use basis.

# 7.5 Data collection

7.5.1 Baseline data

Medical information will be obtained from the medical records and nephrologists in charge before the start of the study: i.e. demographical data, cardiovascular risk factor information, time on dialysis, cause of renal insufficiency, medical history (co-morbidity), and medication. A dedicated case report form to asses baseline data will be provided. This form is designed in teleform, which allows to put the information on the sheet directly into a study database (Teleform). Thus, in principle no data entry by typing is needed.

7.5.2 Recording outcome events

Follow-up will be performed through the nephrologist, since the patients are seen at their clinic 2 or 3 times a week. Every 3 months, the investigators will visit the participating centers, where they will interview the nephrologists personally and review the case records of the patients on the occurrence of CV events or death.

CV events include a fatal or non-fatal myocardial infarction, stroke, lower extremity arterial disease, therapeutic coronary procedure (PTCA/stenting), therapeutic carotid procedure (endarteriectomy/stenting), vascular surgery (revascularisations), and angina pectoris. Congestive heart failure is excluded, since the discrimination with fluid overload is often hard to make.

Furthermore, hospitalisations, the duration of the hospitalisations and main diagnosis (including the occurrence of infections) will be recorded during the study period.

When an event has occurred, the date of the event is being recorded and information on the event is copied from the medical records for review by an event committee. Events will be coded independently from information on the received treatment. Events will be coded as fatal and non-fatal, definite, probable and possible and not codeable (i.e., insufficient information). Only definite and probable events will be used for the analysis. This procedure is currently successfully applied in a number of studies coordinated by the Julius Center, e.g. in the SMART study.[[112]](#endnote-113) Data forms from the SMART study will be used and changed for the current trial if needed.

7.5.3 Observations during HD/HDF

Dry weight and UF volume will be recorded for each treatment, as well as the achieved filtration/substitution dose per treatment.

7.5.4 Left ventricular hypertrophy

Left ventricular mass index (LVMi) will be assessed by echocardiography at baseline, and after 6 months, 12 months and annually afterwards, on a midweek non-dialysis day. Left ventricular end diastolic diameter (LVEDD), left ventricular ejection fraction (LVEF), posterior wall and septal thickness will be determined as well, and recorded on videotape. Videotapes will be evaluated centrally by experienced cardiologists, blinded for the treatment modality.

7.5.5 Vessel wall measurements

With respect to carotid intima-media thickness (CIMT), the outcome is the change in mean common CIMT, defined as the average of the intima-media thickness measurements performed circumferentially at pre-defined angles for the near and far wall of 10 mm segments of the right and left distal common carotid arteries, the far wall of the bifurcation and the far wall of the internal carotid artery. A limited number of centers is going to be involved in the CIMT measurements in this study. Centers will be trained according to a central uniform carotid ultrasound protocol. Before actually starting the study, sonographers need to be certified as outlined in the CIMT ultrasound protocol. Measurements will be performed at baseline and then annually on a midweek non-dialysis day.The ultrasound scan is being recorded on videotape and analyzed off line by a core laboratory. QA/QC procedures as existing and applied in several (inter)national trials will implemented.

Pulse wave velocity (PWV) is determined to provide additional information on functional changes of the arterial wall. The outcome measurement is the change in aortic PWV. A limited number of centers is involved in the PWV measurements in this study. Centers will be trained according to a central uniform PWV protocol. Before actually starting the study, technicians need to be certified as outlined in the protocol. Measurement data are checked regularly on quality control aspects as defined in the protocol (see appendix). Measurements will be performed at baseline and then annually on a midweek non-dialysis day.

7.5.6 Nutritional state

At base-line, after 1, 2 years and at the end of the study, nutritional state is assessed by subjective global assessment (SGA),**[[113]](#endnote-114)** pre-albumin and dry weight.

7.5.7 Quality of life

Patient well-being will be estimated at base-line, and once a year by the Kidney Disease Quality of Life Short Form (KDQOL-SF), which is validated for dialysis patients.**[[114]](#endnote-115)** **[[115]](#endnote-116)**

7.5.8 Laboratory assessments

At base-line, and after 6, 12, 18 months and then annually, blood samples will be drawn from the arterial line before a dialysis session. Patients will be fasting, and the samples will be drawn before the administration of low molecular weight heparin (LMWH). In these samples, the following markers will be assessed:

- routine assessments, as indicated by the DGN: Hb, Ht, phosphate, calcium, parathyroid hormone (PTH); spKt/V urea (monthly), residual renal function (expressed as the mean of urea and creatinin clearance in an interdialytic 24 hour urine collection; every 3 months).
- acute phase response: C-reactive protein (CRP)
- lipid profile: low density lipoprotein (LDL)-cholesterol, high-density lipoprotein (HDL)-cholesterol, Lp(a), triglycerides
- oxidative and carbonyl stress: circulating oxidized low-density lipoprotein (oxLDL), carboxymethyllysine (CML), asymmetric dimethylarginine (ADMA), 2-OH deoxy guanosine, 8-isoprosatane, GSSH/GSH, TBARS
- endothelial dysfunction: von Willebrand factor (vWF), soluble intercellular adhesion molecule (sICAM-1), soluble vascular adhesion molecule (sVCAM-1)
- various: total homocysteine (Hcy), ß2-microglobulin (ß2-m), pre-albumin

A detailed protocol concerning the collection, preparation, processing , short-term and long-term storage as well as archiving is currently being developed. A present citrate, EDTA and serum sample will be stored for later determinations. In addition, buffy-coat will be stored for future research possibilities on the genetic effects on the response to HDF, after permission of the patients (in the informed consent form).

## 7.6 Statistical methods

7.6.1 Primary outcomes

The results of the study will be analysed following the ‘intention to treat’ principle. This means that for the analyses subjects will remain in the group they have been allocated to by the randomisation. Results will be presented as Kaplan-Meier curves for the two treatments and the difference between the treatments will be analysed using a log-rank test. For the primary outcome variables the log-rank test will be adjusted for the effect of the cumulative data analyses. Results will be presented for all cause mortality and CV events separately.

An exploratory analysis will be performed using the ‘on treatment’ approach, i.e., analyses in which subjects are being categorised to the actual treatment they have received.

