# 5. BACKGROUND

# 5.1 Cardiovascular disease in hemodialysis patients: introduction

Cardiovascular disease (CVD) is the most frequent complication and major cause of mortality in dialysis patients,[[1]](#endnote-2) accounting for more than half of all deaths (70% versus 37% in the normal population). In addition, chronic hemodialysis (HD) patients suffer from atherosclerotic complications at a relatively younger age[[2]](#endnote-3) and die younger from ischemic heart disease.[[3]](#endnote-4) The increased cardiovascular (CV) risk is probably multifactorial in origin and already observed in the pre-dialysis phase.

On theoretical grounds, the pathogenetic process leading to CVD can be divided in 4 stages: 1) contributing factors or risk factors; 2) accumulation of ‘uremic toxins’ and disturbances in the balance between oxidants and anti-oxidants and the immuno-inflammatory system; 3) endothelial dysfunction; 4) evidence of atherosclerosis.

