7.6.3 Sample size considerations

7.6.3.1 Primary outcome

The sample size of the present study is based on the following event rates: the 3 year all cause mortality rate among subjects with ESRD is 44% based on RENINE data. CV mortality constitutes 40-60% of the total group of deaths, leading to a 3 year CV mortality rate of 22% in HD patients. Assuming that the incidence of non-fatal CVD is equal to the CV mortality rate (22%), we assume a three year incidence of fatal and non-fatal CVD of 44%. In addition, based on experience around 8% of the ESRD patient will undergo renal transplantation yearly and as such is being censored in the trial.

Assuming that HDF will reduce all cause mortality with 20%, we estimate that with a two-sided alpha of 0.05 and a power of 80%, about 772 patients need to be enrolled and followed for three years. In these patients we expect about 250 events to come to a decision.

Assuming that HDF will also reduce the incidence of fatal and non-fatal CVD with 20%, we estimate that with a two-sided alpha of 0.05 and a power of 80%, the same amount of patients need to be enrolled and followed for three years. (Note that the total number of patients to be included can not be specified in advance because of the planned sequential [interim] analyses.)

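### Kaplan-Meier curves for CV events would overstate the share of patients affected, because non-CV death is about as frequent as CV death on the protocol's own figures

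*Protocol*

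**What the plan says.** Section 7.6.1 (Primary outcomes) fixes both the display and the test: "Results will be presented as Kaplan-Meier curves for the two treatments", with the two arms compared by a log-rank test. It then adds "Results will be presented for all cause mortality and CV events separately", so the same method serves both end points.

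Section 7.3.1 defines the CV end point as "non-fatal and fatal cardiovascular events". A non-CV death is therefore not an event in that analysis.

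Section 7.6.3.1 gives the rates: "the 3 year all cause mortality rate among subjects with ESRD is 44% based on RENINE data", and "CV mortality constitutes 40-60% of the total group of deaths, leading to a 3 year CV mortality rate of 22% in HD patients". Non-fatal CVD is assumed to be as frequent as CV death, which gives a 44% three-year incidence of the composite. A 20% reduction by HDF is assumed for each primary end point. The only censoring named is for renal transplantation, at about 8% a year.

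Section 5.1 gives a different CV share of deaths: "accounting for more than half of all deaths (70% versus 37% in the normal population".

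The protocol nowhere mentions a cumulative incidence function or a competing-risk method.

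**The concern.** A patient who has died of infection or malignancy cannot later have a myocardial infarction. If that death is treated as ordinary censoring, Kaplan-Meier assigns the patient the future CV risk of those still alive. One minus Kaplan-Meier then describes CV risk in a population in which nobody dies of other causes. It does not describe the proportion of patients who have a CV event.

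Where non-CV death is rare the two quantities nearly coincide. Here non-CV death is about as common as CV death, so they separate visibly. The 44% design assumption is itself built as a share of patients (22% plus 22%), so the planned curve would not estimate the quantity on which the design rests.

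At stake are the absolute CV risks and the absolute difference that readers take from the figure for a primary end point. The Summary expects the result to influence practice considerably.

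**Working it through.** **Inputs (section 7.6.3.1).** Control arm: three-year mortality 44%, CV share of deaths 40-60% (midpoint 50%), CV composite 44%. HDF arm: 20% lower, so 0.8 × 44% = 35.2% for each end point.

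**Reproducing the plan's figure.** 0.44 × 0.50 = 22% CV death. Adding 22% non-fatal CVD gives 44%, as stated. Non-CV death is 44% − 22% = 22%. With a 60% CV share it is 17.6%, and with a 40% share 26.4%.

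**Formulas.** Let *a* be the yearly hazard of a first CV event and *b* the yearly hazard of non-CV death before any CV event, both constant over three years.

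- Actual (cumulative) incidence: a/(a+b) × [1 − exp(−3(a+b))]
- Kaplan-Meier complement with non-CV death censored: 1 − exp(−3a)

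The protocol does not say how many non-CV deaths follow a non-fatal CV event, nor whether 44% is an actual or a Kaplan-Meier incidence. I therefore used three readings, first at a 50% share.

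**Reading A: all non-CV deaths precede any CV event, and 44% is the actual incidence.**
- Control: 3(a+b) = −ln(1 − 0.44 − 0.22) = 1.079. 3a = 1.079 × 0.44/0.66 = 0.719. Kaplan-Meier complement = 51.3% against 44.0%, a gap of **7.3 points**.
- HDF (35.2% CV, 17.6% non-CV): 3(a+b) = −ln(0.472) = 0.751. 3a = 0.5005. 39.4% against 35.2%, a gap of **4.2 points**.

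**Reading B: the non-CV hazard is half the all-cause hazard, and 44% is the actual incidence.**
- Control: all-cause hazard −ln(0.56)/3 = 0.1933, so b = 0.0966. Solving for 44% gives a = 0.2301. 49.9% against 44.0%, a gap of **5.9 points**.
- HDF: −ln(0.648)/3 = 0.1446, so b = 0.0723 and a = 0.1637. 38.8% against 35.2%, a gap of **3.6 points**.

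**Reading C: same b as in B, but 44% is already the Kaplan-Meier value.**
- Control: a = 0.1933. Actual incidence = (2/3) × [1 − exp(−0.870)] = 38.7%, a gap of **5.3 points**.
- HDF: a = 0.1446. Actual incidence = (2/3) × [1 − exp(−0.651)] = 31.9%, a gap of **3.3 points**.

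**Overstatement in percentage points, by CV share of deaths:**

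| CV share | Control A / B / C | HDF A / B / C |
|---|---|---|
| 40% | 9.3 / 7.0 / 6.2 | 5.2 / 4.3 / 3.9 |
| 50% | 7.3 / 5.9 / 5.3 | 4.2 / 3.6 / 3.3 |
| 60% | 5.5 / 4.7 / 4.3 | 3.2 / 2.9 / 2.7 |
| 70% (section 5.1) | 3.9 / 3.5 / 3.3 | 2.3 / 2.2 / 2.0 |

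**Absolute difference between arms, 50% share.**
- A: displayed 51.3 − 39.4 = 11.9 points, against an actual 44.0 − 35.2 = 8.8.
- B: displayed 49.86 − 38.81 = 11.05, about 11 points, against 8.8.
- C: displayed 8.8 points, against an actual 38.73 − 31.89 = 6.8.

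The displayed benefit is thus inflated by a quarter to a third or slightly more (11.05/8.8 = 1.26; 8.8/6.84 = 1.29; 11.9/8.8 = 1.35).

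**The case against.** **The inference is untouched.** The analysis that decides the trial is the log-rank test, and with non-CV death censored it remains a valid comparison of cause-specific hazards. This stands. A reader might infer that the primary test, or the mortality end point, is compromised. The documents do not support that: all-cause mortality is reported separately and has no competing death. The fault is confined to the displayed CV incidence and its difference.

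**No single figure is justified.** This also stands. A reader might settle on about 7 points by taking the non-CV hazard as −ln(0.56)/3 − [−ln(0.78)/3] = 0.110 a year, which gives 50.7% against 44%. But the 22% CV mortality is a crude share of deaths, and that step treats it as a net risk. The resulting hazard is 0.110/0.193 = 57% of the all-cause hazard, not half. With half, the gap is 5.9 points. A gap of 7.3 needs every non-CV death to come before any CV event. Both are control-arm values, and with the 70% share of section 5.1 the gap is only about 3-4 points.

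**Transplantation.** A reader might wish to treat it as a competing event too. Section 7.6.3.1 censors it, and changing that is a choice of estimand, not the correction of an error.

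**This could be left to an analysis plan.** In part. Section 7.6.1 does not say in words that non-CV death is censored; that follows from using Kaplan-Meier for an end point that excludes it. But the protocol does more than stay silent: it names the estimator for a primary end point, and nothing elsewhere qualifies it.

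**Conclusion.** The point holds as a fault of display. With non-CV death censored, the planned CV curves overstate the actual three-year incidence by about 4-9 points in the control arm over a 40-60% CV share, and by about 3-4 points in the HDF arm at a 50% share. With the 70% share of section 5.1 the figures are about 3-4 and about 2 points. The displayed absolute benefit would be about 11-12 points where the planned reductions imply 8.8.

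These sizes rest on constant hazards and on HDF lowering CV and non-CV events alike by 20%; a different effect on non-CV death would change the distortion of the difference. The direction of the overstatement within an arm does not depend on these assumptions. It should be corrected before reporting, but it does not threaten the primary test.

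**What to change.** In section 7.6.1, separate the two end points.

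- **All-cause mortality:** keep Kaplan-Meier and the log-rank test.
- **CV events:** present Aalen-Johansen cumulative incidence curves by arm and the three-year risk difference with its confidence interval, with non-CV death as the competing event.
- Show the cumulative incidence of non-CV death by arm beside them.
- Keep the log-rank test for CV events and state that it compares cause-specific hazards, with non-CV death censored for that test.
- Keep transplantation censored, as section 7.6.3.1 states.

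The cost is one standard additional analysis and a few sentences of text. Event dates are recorded (section 7.5.2) and the event committee already reviews cause of death (section 10.4), so no new data are needed. Sample size and sequential monitoring need no change on this account.

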## 5.2 Pathogenesis of cardiovascular disease in HD patients

5.2.1 contributing factors

Several conventional risk factors are known to contribute to the increased prevalence and incidence of CVD in chronic HD patients, some being -at least partly- modifiable (smoking, hypertension, dyslipidemia, diabetes), and others not (age, gender). Frequently, a combination of these factors is present, that may explain the high prevalence of CVD in this patient group.[[4]](#endnote-5) Moreover, an impaired renal function per se appears to be a risk factor as well.[[5]](#endnote-6) In this respect, the accumulation of several uremic substances, such as homocysteine and Lp(a), may play an important role. In addition, it has been suggested that HD treatment itself contributes to the micro-inflammatory state that is commonly observed in chronic HD patients (see below).3

5.2.2 accumulation of ‘uremic toxins’

Apart from urea and creatinin, a variety of ‘uremic toxins’ has been described in CRF.[[6]](#endnote-7)

Nitric oxide (NO) inhibits key processes in atherosclerosis, such as monocyte adhesion, platelet aggregation and smooth muscle cell proliferation. It has been shown that chronic HD patients exhibit reduced NO levels, as well as an accumulation of *asymmetric dimethylarginine (ADMA),* an endogenous inhibitor of NO-synthase. [[7]](#endnote-8) In fact, ADMA appeared to be a strong predictor of CV events and total mortality in this patient group.[[8]](#endnote-9)

Apart from a characteristic atherogenic *lipid profile*, including low concentrations of high-density lipoprotein (HDL)-cholesterol, chronic HD patients exhibit elevated triglyceride, intermediate density lipoprotein (IDL)-cholesterol and Lp(a) concentrations.[[9]](#endnote-10) In observational studies it was shown that in particular the latter abnormality was related to the presence of CVD in these patients. [[10]](#endnote-11)

*Homocysteine* (Hcy) is an amino-acid that is produced by the demethylation of methionine. Hcy levels are increased in HD patients, whereas Hcy appeared to be an independent risk factor for CVD in both renal and non-renal patients.[[11]](#endnote-12) [[12]](#endnote-13) [[13]](#endnote-14) Thus far, it proved difficult to show clinically relevant effects of Hcy lowering therapy. Recently however, it was shown that reduction of Hcy decreased the incidence of restenosis after coronary angioplasty in a non-renal population.[[14]](#endnote-15)

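### The primary log-rank test uses no baseline covariates although prognostic data are collected before the start; the test is valid, but it gives up some efficiency that could be recovered cheaply

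*Protocol*

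**What the plan says.** Section 7.6.1 sets an intention-to-treat comparison in which "the difference between the treatments will be analysed using a log-rank test". It names one adjustment: "the log-rank test will be adjusted for the effect of the cumulative data analyses". That concerns the sequential looks, not patient characteristics. The same test serves all-cause mortality and cardiovascular (CV) events, which are reported separately.

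Section 7.5.1 lists what is obtained before the start: "demographical data, cardiovascular risk factor information, time on dialysis, cause of renal insufficiency, medical history (co-morbidity), and medication". Age falls under the first item. Diabetes and previous CV disease fall under risk factors and medical history.

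Section 5.2.1 says that "Several conventional risk factors are known to contribute to the increased prevalence and incidence of CVD in chronic HD patients". Age and diabetes are among its examples, but it gives no strength of association for any factor. Section 7.1.1 sets no upper age limit and cites, for Europe, a median age of 60 at the start of haemodialysis (HD), with "proportion of new HD-patients 60-69 yr: 25%, >70 yr: 27" per cent.

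For the sample size, section 7.6.3.1 states that "the 3 year all cause mortality rate among subjects with ESRD is 44% based on RENINE data" and, for the other end point, "we assume a three year incidence of fatal and non-fatal CVD of 44" per cent. Both are paired with a 20% reduction, two-sided alpha 0.05, 80% power, 772 patients, about 250 events and 8% per year censored at transplantation.

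**The concern.** When patients differ widely in baseline hazard, a log-rank test compares groups of mixed risk. In a survival model, leaving out strong predictors pulls the treatment contrast towards the null even under perfect randomisation. A score test for treatment from a model that holds those predictors still tests the randomised comparison, and it has more power at the same number of events.

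This population is likely to be heterogeneous, because adults of any age can enter and several predictors are named. The data are already on the baseline form. At stake is the chance of detecting a real 20% reduction, or the number of looks needed before a boundary is crossed.

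The protocol names both the test and its one adjustment. An analysis plan that made an adjusted test primary would therefore depart from it. The point concerns patient-level predictors and is separate from stratifying the test by clinic.

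**Working it through.** **Inputs from the protocol.** Control risk 44% at 3 years, 20% reduction to 35.2%, 772 patients randomised 1:1 (386 per arm), 8% per year censored, two-sided 5% (7.6.3.1, 7.2.2).

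**The plan's own figure first.** With exponential survival, HR = ln(0.648)/ln(0.56) = 0.748.

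- Events for 80% power (Schoenfeld): 4 × (1.960 + 0.842)² / (ln 0.748)² = 374.
- With a censoring hazard of 0.08 per year, the probability of an observed death is 0.396 on HD and 0.316 on hemodiafiltration, mean 0.356. So 374 events need about 1,052 patients.
- 772 patients yield 772 × 0.3557 = about 275 events. The drift is √(275/4) × 0.290 = 2.40, and power is Φ(2.40 − 1.96) = 67%.

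The stated 772 and 250 therefore do not reproduce as a fixed two-sided design. They are 73% and 67% of 1,052 and 374. They may be expected values under the double triangular test, but the boundaries are not given and this cannot be checked. The 67% is used below only as a fixed-test reference.

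**Assumed prognostic strength.** The protocol gives none, so it is varied as the SD of the log-hazard across patients. For orientation, 27% above 70 with a median of 60 implies, under normality, an age SD of (70 − 60)/0.613 = 16.3 years. A hazard ratio h per decade then gives a log-hazard SD of 1.63 × ln h, for example 1.63 × ln 1.4 = 0.55.

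**Simulation for mortality.** 386 per arm, one normal covariate, risks calibrated to 44% and 35.2%, censoring hazard −ln(0.92) per year, end at 3 years, fixed two-sided 5% test, 10,000 trials per row. The last column spans this run and two repeats with separate code.

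| Log-hazard SD | Equivalent age HR per decade | Log-rank power | Adjusted power | Gain (points) | Gain across runs |
|---|---|---|---|---|---|
| 0.30 | 1.2 | 66.3% | 68.1% | 1.8 | 1.1 to 1.8 |
| 0.43 | 1.3 | 67.3% | 70.9% | 3.6 | 3.2 to 3.6 |
| 0.55 | 1.4 | 68.1% | 73.4% | 5.3 | 4.9 to 5.4 |
| 0.66 | 1.5 | 68.4% | 76.3% | 7.9 | 7.5 to 8.7 |
| 0.80 | combined score | 68.8% | 80.0% | 11.2 | 11.2 to 12.8 |

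Under the null at 1.4 per decade, the rejection rate was 4.9% unadjusted and 4.8% adjusted.

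**Cross-check by formula.** If the covariates explain a share R² of the prognostic variation, power is about Φ(2.40/√(1 − R²) − 1.96). From 275 events this gives gains of 2.2, 4.6, 9.5 and 12.1 points at R² of 0.05, 0.10, 0.20 and 0.25, the same range as the table.

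**Dependence on the starting point.** With 1,052 patients, where the log-rank test already has about 80% power, the simulated gains are about 2, 4 and 7 points at log-hazard SD 0.3, 0.5 and 0.7.

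**The case against.** The strongest reply is that nothing here is wrong. The log-rank test is valid, it matches the Kaplan-Meier display, and it is a standard basis for a sequential survival test. Covariate lists are often left to an analysis plan. The first part stands: this is a question of efficiency. The second stands only in part, because 7.6.1 already fixes the test and its single adjustment.

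Other limits also stand:

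- **Size.** A reader might infer a fixed loss, say 4 to 11 points. From a nominal 80% that needs an assumed R² of about 0.10 to 0.28, and the protocol has no figure to support it. The age SD is also weak. It comes from one quantile for European patients starting HD, whereas the trial enrols patients already on HD, whom 7.1.1 describes as older still.
- **Both end points.** A reader might carry the figures over to CV events, since 7.6.3.1 assumes the same 44% and 20%. That was not computed. By the protocol's own figures, 44% − 22% = 22% would die of non-CV causes within 3 years, which ends follow-up for CV events, and the covariates may predict those events better or worse than death.
- **Design.** The figures are for a single-look test. Section 7.6.4 plans sequential looks on data supplied every two months, so part of the gain may come as earlier stopping.
- **Secondary models.** A reader might see an inconsistency with 7.6.2. The contrast is weak: the main carotid thickness model holds visit days, treatment and centre, baseline thickness is exploratory, and the pulse wave velocity adjustments are changes after baseline.
- **Robustness.** The null check used one setting with a correct model and censoring unrelated to the covariate. Misspecification and covariate-dependent transplantation were not tested.

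**Conclusion.** The point holds as a cheap improvement. Section 7.6.1 fixes a valid but unadjusted primary test while prognostic data are already collected. For mortality, with 772 patients and a fixed two-sided 5% test, adjustment would add about 1 to 2 points of power if the baseline score is weak (log-hazard SD 0.3), about 3 to 8 if moderate (0.43 to 0.66) and about 12 if strong (0.8).

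The direction is secure whenever the covariates predict the outcome. The size rests on strengths that the protocol does not give. The documents do not support reading this as a type I error fault, as a known loss for both end points, or as proof that the trial's power is 67%, because the sequential boundaries are not shown.

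**What to change.** Before the first interim look, state in 7.6.1 that the primary test of each primary end point is the treatment score test from a Cox model adjusted for a short fixed list: age as a continuous variable, diabetes, history of CV disease and time on dialysis. State in 7.6.4 that the sequential test uses the score and information from that same model. Keep the unadjusted log-rank test and the Kaplan-Meier curves as supportive.

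The cost is wording in two sections and four baseline items added to the two-monthly dataset, which must be complete for every patient. The reported hazard ratio becomes conditional on the covariates. At log-hazard SD 0.7, for example, the conditional ratio is 0.72 where the ratio calculated from the 3-year risks is 0.748, so the report should say which one it gives. No extra patients or visits are needed. A change of test after looks have begun would be open to challenge.
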